### Safety Considerations

Before enrolling in the study, all participants will be screened for possible rTMS contraindications (seizure history, brain lesions, metallic implants, etc). Participants will be asked at each visit if they have experienced any adverse effects from the treatment. Any reported adverse events or effects will be recorded, and treatment will be suspended at the discretion of the study physicians if the adverse effect is considered to be serious (ie, life threatening or requiring hospitalization or medical treatment). The participant’s self-assessment of any pain or discomfort from the treatment will also be recorded at every visit.

A data and safety monitor board (DSMB) will oversee the study to ensure that proper safety procedures are followed and that adverse effects of the treatment are properly documented. If adverse effects are discovered that warrant a review or investigation before proceeding with the study, the DSMB will have the authority to initiate such a review. The DSMB will also ensure that the study does not deviate from the intended protocol.

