### Outcome Measures

Each participant will attend six assessment days in total as follows: baseline (week 0) and week 3, week 5, week 8, week 16, and week 24 posttreatment sessions. At each assessment day, three assessments will be given to the participant in the following fixed sequence: ADAS-Cog, verbal fluency test, and Stroop test. Only the patient and the research personnel designated to administer assessments will be in the room during assessments. At the baseline and week 5 and week 16 posttreatment assessments, additional caregiver assessments will be performed. Alzheimer Disease Co-operative Study-Activities of Daily Living Inventory (ADCS-ADL) and Neuropsychiatric Inventory Questionnaire (NPI-Q) assessments will be performed at each of these visits (in that order), while the Treatment Satisfaction Questionnaire for Medication (TSQM) will only be used at the week 5 assessment. These outcome measures must be administered to the same caregiver at each visit. If a participant is accompanied to an assessment visit by someone other than their usual caregiver, the assessor will contact the usual caregiver by phone to complete these assessments.

All assessments will be performed on a Monday or the first working day of the week. Note that the specific dates of the last three assessments (the follow-up assessments) will be adjusted based on whether the participant is in a 2-week or 4-week treatment group. An assessor will be assigned to each participant. That same assessor must perform all of the six assessments with the assigned participant. Deviations should be justified (changes in staff, assessor illness, etc), and an explanation will be documented in the assessment notes.

As participant schedules are often busy, we can adjust the specific dates of the assessments within ranges (Table 1). If no assessment is possible within these windows, the assessment will be skipped and the data point will be missing from the analysis (with the exception of the baseline assessment, which will require rescheduling the treatment).

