## Results

### Recruitment and Enrollment

As of November 1, 2020, we have screened 523 individuals, out of which 133 were eligible and have been enrolled. Out of the 133 individuals enrolled and randomized to the intervention groups, 104 have completed the study and 20 have discontinued the study or have withdrawn for various reasons at various stages of the study. Data of some withdrawn individuals who completed the study up to week 8 or 16 are still usable for analysis. Three individuals withdrew because they found the treatment uncomfortable, nine withdrew with no reason given, and eight were withdrawn by the site PI. Out of the eight withdrawn by the site PI, two were withdrawn for safety reasons as they developed some illnesses, although they were not related to the rTMS treatment, four were noncompliant (changed their medication during the study) or found the rTMS pulses unbearable, and two could not finish the treatment due to pandemic lockdown.

Recruitment and enrollment have been slower than initially anticipated, and the pandemic has slowed these even further. Before the pandemic, the realistic recruitment rate was one per month.

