### Adverse Events

We have developed a series of detailed questions to mark any plausible adverse effect of the treatment, and the series is used consistently among the different sites of the study. As of November 1, 2020, there has been no serious adverse event. However, 89 of the participants reported expected adverse events as described in the Plausible Side Effects section above. Twelve participants reported some unexpected adverse events, which were most likely unrelated to the rTMS treatment. The reported events were increased blood pressure on one day, a nightmare, vivid dreaming, sleeping trouble, disorientation, blurry vision, and unsteadiness on the feet for a few minutes. All reported cases were temporary and reported on only one day. All issues resolved without medication. All adverse events have been described in detail in quarterly DSMB reports.

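### The stated adverse-effect question goes to participants with dementia and is tied to the treatment, and two illness withdrawals are not reconciled with the reported zero serious events

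*Protocol article*

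**What the plan says.** **How events are elicited.** Safety Considerations says: "Participants will be asked at each visit if they have experienced any adverse effects from the treatment". It continues: "Any reported adverse events or effects will be recorded". The Adverse Events section adds: "We have developed a series of detailed questions to mark any plausible adverse effect of the treatment", and says the same series is used at all sites.

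**Who is asked.** The inclusion criteria under Recruitment admit a CDR of 1 to 2 and a MoCA of 7 to 25. Treatment Protocol keeps the caregiver out of treatment sessions as a measure against unblinding. Outcome Measures says: "Only the patient and the research personnel designated to administer assessments will be in the room during assessments". Caregivers are contacted at baseline, week 5 and week 16 for the ADCS-ADL and NPI-Q, by phone if someone else accompanies the participant. The TSQM is added at week 5. No adverse-event question to the caregiver is described.

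**What counts as serious.** Safety Considerations lets the study physicians suspend treatment "if the adverse effect is considered to be serious (ie, life threatening or requiring hospitalization or medical treatment".

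**What is reported.** Recruitment and Enrollment says that, of eight participants withdrawn by site investigators, "two were withdrawn for safety reasons as they developed some illnesses, although they were not related to the rTMS treatment". Adverse Events says: "As of November 1, 2020, there has been no serious adverse event". It reports expected events in 89 participants and unexpected events, judged most likely unrelated, in 12. It describes the reported cases as temporary, confined to one day and resolved without medication.

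**The concern.** There are two separate issues.

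First, the stated prompt asks a person with impaired memory both to recall an event and to attribute it to rTMS. An event that is forgotten, or put down to something else, may never be mentioned and so never reach the record. The protocol relies on the caregiver for function and behaviour but does not name the caregiver as a source for safety.

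Second, three sections do not fit together. Two illnesses led to withdrawal for safety, yet no such illness appears among the unexpected events described. Relatedness does not explain the gap consistently, because other events judged most likely unrelated are counted.

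At stake is the statement of zero serious events. The abstract repeats it, alongside an expectation that rTMS will have no serious side effect, and adverse events are described in the quarterly DSMB reports. The primary efficacy analysis is not affected.

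**Working it through.** **1. Check that the counts add up** (Recruitment and Enrollment).
- Withdrawals or discontinuations: 3 + 9 + 8 = 20.
- Withdrawn by site investigators: 2 + 4 + 2 = 8.
- Still in the study: 133 − 104 − 20 = 9.
- Expected events: 89/133 = 67%. Unexpected events: 12/133 = 9%.

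The totals are consistent, so the problem is not arithmetic.

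**2. Where recall matters** (Treatment Protocol; Outcome Measures, Table 1).
- During treatment, visits run 5 days a week, so recall covers a day or a weekend.
- In late follow-up, the scheduled gaps are 16 − 8 = 8 weeks and 24 − 16 = 8 weeks.
- With the ±2-week windows, the last gap can reach (24 + 2) − (16 − 2) = 12 weeks.
- The last scheduled caregiver contact is at week 16.

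**3. Set the reports side by side.**

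| Section | Content |
|---|---|
| Safety Considerations | Serious includes needing medical treatment; the wording is attached to an adverse effect and to suspension of treatment |
| Recruitment and Enrollment | Two illnesses led to withdrawal for safety, judged unrelated |
| Adverse Events | No serious adverse event; unexpected events were raised blood pressure on one day, dreams or sleep problems, disorientation, blurred vision and brief unsteadiness |
| Plausible Side Effects | Expected effects are headache, toothache and pain in the eye, scalp and neck, plus seizure risk |

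The two illnesses are in neither list in any recognisable form. Their nature, duration and treatment are not given.

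**4. Size of the uncertainty in the count.** A reported zero has no design formula to reproduce, so only its precision and the alternatives can be shown (n = 133).
- If neither illness qualifies: 0/133. Two-sided 95% upper limit = 1 − 0.025^(1/133) = 2.7%.
- If one qualifies: 1/133 = 0.8%.
- If both qualify: 2/133 = 1.5%. Exact 95% limits are the Beta(2, 132) quantile at 0.025 = 0.2% and the Beta(3, 131) quantile at 0.975 = 5.3%.

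**5. Can the zero itself show that capture was complete?** The documents give neither a true serious-event rate p nor a captured share s, so both are assumed here. The chance of seeing none is (1 − p·s)^133.

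| Assumed p | All captured (s = 1) | Half captured (s = 0.5) |
|---|---|---|
| 1% | 26% | 51% |
| 3% | 1.7% | 13% |
| 5% | 0.1% | 3.5% |

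A zero fits either a low true rate or incomplete capture. The figures cannot separate the two.

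**The case against.** The strongest reply is that an article need not reproduce the adverse-event form, and that much of the suspicion rests on silence. Several stronger readings that a reader might infer do fail.

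- *Only patients can report.* No section excludes reports from caregivers or staff. The rules about who is in the room concern treatment and testing, and caregivers also complete the TSQM.
- *Events are filtered by attribution before they are counted.* Any reported event is recorded, and 12 participants with events judged most likely unrelated were counted. The weakness lies in what is asked, not in what is recorded once mentioned.
- *Recall is poor throughout.* Treatment visits are nearly daily. The long gaps belong to late follow-up.
- *The comparison of active with sham is biased.* Participants are blind and the same questions are used at every site. Under-reporting would reduce sensitivity, but the documents show no mechanism that differs by arm.
- *The zero is wrong.* The illnesses may have needed no treatment, or may have ended participation by meeting an exclusion criterion or a TMS contraindication. The wording on seriousness sits in the rule for suspending treatment and speaks of an adverse effect, so it may not be the definition behind the count of adverse events. The DSMB reports, which are said to give detail, are not shown.

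Two things remain. The prompt is a stated rule, not an omission, and it ties the question to the treatment. The article also gives only one meaning of serious and does not say whether the two illnesses were assessed against it or against another.

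**Conclusion.** The concern holds in two limited parts. The stated question, put to people with mild to moderate dementia and tied to the treatment, with no caregiver source named, invites under-reporting, mainly in follow-up. The extent cannot be estimated from the documents. Separately, the zero is not secured, because two safety withdrawals for illness are not reconciled with the event descriptions or with the wording of serious. On 133 enrolled, the count is 0 (upper limit 2.7%) or as high as 2 (1.5%, CI 0.2% to 5.3%) on account of these two participants. The higher figure assumes that both illnesses met the wording in Safety Considerations, which the documents neither state nor rule out. The intervals overlap widely, so what is in doubt is the accuracy of a flat statement of zero; no safety signal is shown.

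**What to change.** - Word the question as any new or worsened health problem, whatever its cause, within the existing question series. Judge relatedness afterwards.
- Put the same question to the caregiver at the contacts already scheduled, by phone where needed. Those contacts end at week 16, so a short call at week 24 would be an addition, worth considering because it covers the last long gap.
- Use one definition of serious for counting and reporting, applied irrespective of relatedness. Say whether the wording in Safety Considerations is that definition. The rule for suspending treatment is a clinical matter and is not addressed here.
- Assess the two illness withdrawals under that definition, reconcile Safety Considerations, Recruitment and Enrollment, and Adverse Events, and restate the count in the text and abstract if it changes.
- Note the date on which the wording changes, so that events elicited before and after can be told apart.

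The cost is a revised form, a few more minutes per caregiver contact and a review of two case records. The downside is small: more unrelated events will be recorded, and the interim safety statement may become less favourable.

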### Ethical Considerations and Follow-Up

Following the 24-week posttreatment assessment, participants will be informed of their assigned treatment group. Patients randomized to the sham treatment will be offered 2 weeks or 4 weeks of active treatment. The patients and/or their family can choose the duration of treatment. Any participant who experiences an adverse effect will be followed up by a study physician until the adverse effect has resolved.

### Data Management

Study data (participant medical and demographic data, treatment records, and assessment results) will be maintained on a password-protected database accessible only to active research team members, with access to specific information, such as group assignment, and assessment results restricted based on the individual’s assigned role in the study. Regular backups of the database will be performed and stored on a secure server. Identifying information (name, phone number, address, etc) will not be stored on the same system as the study data and will only be accessible to staff members who need to contact participants.

### Statistical Analysis

#### Sample Size Estimation

The sample size for the hypothesis that one group’s mean is statistically significantly different from the other (assuming two equally sized groups, which is the case in this study) can be calculated using the following formula [55]:

where *Z_α_* is the upper tail critical value in the standard normal distribution at the α level of significance (it is 1.96 and 2.58 for 5% and 1% significance levels, respectively), *Z_β-1_* is the normal deviate at 1−β% power with β% of type II error (it is 0.84 and 1.28 for 80% and 90% power, respectively), and *σ* and *d* are the standard deviation and difference of means of the two groups, respectively. The calculated N is the number of subjects in each group.

Using the above formula with a significance level of .05 (corrected using the Bonferroni adjustment for three treatment groups), an expected difference of 3 points on the ADAS-Cog score (derived from a study by Rabey et al [7], which also used ADAS-Cog as a primary outcome measure), a standard deviation of 4.9 points (derived from the results of our own pilot study [8]), and a power level of 80%, the minimum sample size is estimated to be 63 participants per group (189 in total). Allowing for 10% drop out, we will need to enroll at least 208 patients in the study to achieve this power.

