**Objective:**

The objectives are to (1) recruit and enroll up to 200 eligible participants, (2) estimate the difference in treatment effects between active treatment and sham treatment, (3) estimate the difference in treatment effects between two doses of rTMS applications, (4) estimate the duration of treatment effects among responders to active rTMS treatment, and (5) estimate the effect of dementia severity on treatment outcomes among patients receiving active rTMS treatment.

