## Methods

### Recruitment

Recruitment for this study will be performed at all three sites. Patients with probable Alzheimer disease at mild to moderate stages will be recruited. The target recruitment rate of patients at each site is estimated to be approximately 25 per year, with a target total recruitment of 300 participants across all sites.

All potential participants must have been diagnosed with mild or moderate stage Alzheimer disease by their referring physician or one of our study doctors. The screening doctor will complete an eligibility assessment with the potential participants to confirm their suitability to participate in the study. This assessment will use the CDR [49] and MoCA [50] to assess the severity of dementia. In addition, they will complete the Cornell Scale for Depression in Dementia (CSDD) [51] to assess for comorbid depression. The screening doctor will also consider various inclusion and exclusion criteria.

The inclusion criteria are as follows (all must be met): age >55 years; MoCA score between 7 and 25; CDR score of 1 to 2; CSDD score of 18 or less to rule out moderate to severe depression; diagnosis of probable mild or moderate Alzheimer disease as confirmed by the treating neurologist, geriatrician, or psychiatrist, and/or by the study coinvestigators; and use of a stable dose or no dose of an acetylcholinesterase inhibitor for at least 3 months prior to study entry with no plans to change medication for the duration of the study. If a participant decides to discontinue an Alzheimer disease–related medication (ie, a cholinesterase inhibitor), he/she will wait a minimum of 6 weeks prior to the start of the rTMS treatment.

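### The 63 per group does not follow from the stated Bonferroni-corrected inputs, which give 56 to 58, and the article carries three incompatible enrolment figures (200, 208, 300)

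*Protocol article*

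**What the plan says.** Under Sample Size Estimation, the protocol article compares two equally sized groups. The inputs are "a significance level of .05 (corrected using the Bonferroni adjustment for three treatment groups"), a difference of 3 ADAS-Cog points, a standard deviation of 4.9 and 80% power. For the critical value the section lists two numbers: "it is 1.96 and 2.58 for 5% and 1% significance levels, respectively". It concludes that "the minimum sample size is estimated to be 63 participants per group (189 in total"), and then: "Allowing for 10% drop out, we will need to enroll at least 208 patients in the study to achieve this power".

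Two other places in the current text give an enrolment figure:

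- The Objective in the Abstract is to "recruit and enroll up to 200 eligible participants".
- The Recruitment section plans for 25 patients per site per year, "with a target total recruitment of 300 participants across all sites".

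The interim analysis section plans a look after 150 are enrolled. One of its questions is whether the trial would reach its objective if continued to its planned maximum size. Under Recruitment and Enrollment, of 133 enrolled by November 1, 2020, "104 have completed the study and 20 have discontinued the study or have withdrawn for various reasons".

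**The concern.** There are two separate defects.

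First, the per-group number cannot be recovered from the inputs printed beside it. It matches the 1% critical value listed in the same section, so a reader cannot tell which per-comparison alpha the trial was sized for.

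Second, a ceiling of 200 and a floor of 208 cannot both be met. A target of 300 satisfies the floor but breaks the ceiling. This matters for a trial still recruiting: the interim question depends on the planned maximum, and with recruitment reported as slower than expected, the enrolment figure decides when the trial stops.

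**Working it through.** **Inputs** (Sample Size Estimation): d = 3, σ = 4.9, Zβ = 0.84 for 80% power, family-wise alpha .05 divided by 3. The tests are read as two-sided, because 1.96 is paired with 5% and 2.58 with 1%. Three equal arms follow the Experimental Design section. The formula itself is not shown, so the standard form is assumed:

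n per group = 2(Zα + Zβ)²σ²/d², with 2σ²/d² = 2 × 24.01/9 = 5.3356.

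**1. Reproducing the stated figures.** With Z = 2.58: 5.3356 × (2.58 + 0.84)² = 5.3356 × 11.696 = 62.4, so 63. Then 3 × 63 = 189, and 189 × 1.10 = 207.9, so 208. All the printed figures come back, but at the 1% level, which is .05/5 rather than .05/3.

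**2. The stated inputs.** .05/3 = .0167 two-sided gives Z = 2.394: 5.3356 × (2.394 + 0.84)² = 5.3356 × 10.459 = 55.8, so 56. The smallest n with 80% power under the noncentral t distribution is 58.

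**3. Other readings at d = 3, σ = 4.9.**

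| Alpha | Sides | Power | n per group |
|---|---|---|---|
| .05 | 2 | 80% | 42 |
| .025 | 2 | 80% | 51 |
| .05/3 | 1 | 80% | 48 |
| .05/3 | 2 | 80% | 56 |
| .01 | 2 | 80% | 63 |
| .05/3 | 1 | 90% | 63 |

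The last row also gives 63, but it contradicts the stated 80% power.

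**4. Power of 63 per group at .05/3.** 85.1% by the normal formula, 84.2% by t.

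**5. Enrolment at 10% loss.** 168/0.90 = 186.7, so 187. 174/0.90 = 193.3, so 194. If 63 per group is kept, 189/0.90 = 210, against the stated 208, which leaves 208 × 0.90 = 187.2 evaluable.

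**6. Power of each enrolment figure after 10% loss** (normal formula, three equal arms):

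| Enrolled | Evaluable per arm | Alpha .05/3 | Alpha .01 |
|---|---|---|---|
| 200 | 60 | 83.1% | 78.2% |
| 208 | 62.4 | 84.8% | 80.1% |
| 300 | 90 | 95.7% | 93.7% |

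By t, 60 per arm gives 82.1% at .05/3 and 76.7% at .01.

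**7. What the three figures mean at the interim look.** 150 enrolled is 75% of 200, 72% of 208 or 50% of 300. From 133 enrolled, 67, 75 or 167 patients remain.

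**8. Discontinuation so far.** 20/(104 + 20) = 16.1% of those whose course has ended, and 20/133 = 15.0% of all enrolled. If 16.1% were the loss for the primary endpoint, 208 enrolled would leave 208 × 104/124 = 174.5, about 58 per arm. At .05/3 that gives 81.7% power by the normal formula and 80.6% by t. 200 enrolled would leave 167.7, about 56 per arm, with 80.1% and 78.9%.

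**The case against.** The strongest reply is that nothing is lost. At the stated alpha the plan asks for more patients than it needs, and all three enrolment figures exceed 80% power after the planned 10% loss. That stands, and it limits the point to a wrong derivation and an inconsistent enrolment figure.

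Four stronger readings are tempting, and the documents do not support them.

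- **The stated power belongs to no defined trial.** A reader might infer this from the three targets. But the Sample Size Estimation section ties the power explicitly to 208 enrolled.
- **The trial is underpowered, at 73 to 77%.** These figures need a 1% test. No section plans one: the sample-size text names .05 with a Bonferroni correction, and Analysis of the Results sets significance at .05. The 2.58 is inferred from the arithmetic.
- **Actual attrition is 16%, so the 10% assumption is already refuted.** The 20 discontinuations cover the whole study to week 24, and two were caused by the pandemic lockdown. The primary outcome is the change from pretreatment to posttreatment, some withdrawn participants are said to have usable data, and missing values are carried forward. The article does not say how many lack the primary endpoint, so 15 to 16% is an upper bound.
- **208 instead of 210 is a material error.** Multiplying by 1.10 rather than dividing by 0.90 is the wrong operation, but the gap is two patients.

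It is also fair to say that only the 200 is worded as a maximum, while 208 is a minimum and 300 a target. That does not reconcile them, since the minimum exceeds the maximum.

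**Conclusion.** The point holds in two parts. First, 63 per group (189) is wrong as a consequence of the stated inputs: they give 56 (168), or 58 (174) by t, and 63 corresponds to a two-sided 1% level. The discrepancy is 5 to 7 patients per group in the conservative direction, so the true power at .05/3 is about 84 to 85% rather than 80%. Second, 200, 208 and 300 cannot all describe this trial, which leaves the planned maximum in the interim analysis without a single value.

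At the stated alpha no loss of power is shown at the planned 10% dropout. Even at the 16% upper bound, 208 enrolled keeps about 81%. The power would fall below 80% at 10% loss only if a 1% level was really intended and enrolment stopped at 200 (about 77 to 78%), or, by t, if 208 were enrolled at that level (62.4 per arm, 78.8%).

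This rests on the standard two-mean formula, two-sided testing and three equal arms. The interim section's four arm labels (G1 to G4) do not match the three arms of the Experimental Design section. They would need their own reconciliation before these powers could be applied to a four-arm trial.

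**What to change.** 1. State the per-comparison alpha and the Z value used. If it is .05/3 (Z = 2.394), either restate n as 56 per group (58 by t) or keep 63 and restate the power as about 84 to 85%. If a 1% level was intended, say so and why, and note that 200 enrolled with 10% loss then gives about 77 to 78%.
2. Inflate for dropout by 1/(1 − dropout).
3. Give one enrolment figure in the Objective, Recruitment and Sample Size Estimation sections, and name it as the planned maximum for the interim analysis, before that analysis is run. Keeping 208 is acceptable: with 58 per arm by t (174 evaluable), it covers a loss of up to 16%.
4. Report the 15 to 16% whole-study discontinuation as an upper bound on primary-endpoint loss, and add the number of participants who actually lack the posttreatment ADAS-Cog.

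The cost is wording only. Keeping 208 adds no patients to what the sample-size section already requires.
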